### Sample size estimation

2.2

The sample size was estimated based on the primary outcome of the study “the evaluation of the difference in gait assessed by the Tinetti Performance-Oriented Mobility Assessment gait (POMA-G) scale (36) between the TT+AVR and the TT group at T1.” Data for the estimation were obtained from a previous study aiming to evaluate the effects of non-conventional TT (partial weight-supported TT) on patients with PD (37) using the POMA-G scale. Mean values observed in the POMA-G score after 4 weeks of treatment were 10.7 ± 1.1 and 11.7 ± 0.5, for the conventional gait training and partial weight-supported TT group, respectively, leading to a high effect size *d* = 1.17. Based on those data and assuming a statistical power of 95% and an *α* = 0.05, the resulting sample was 20 subjects per arm. Dropouts are expected to be around 20%. To compensate for possible dropouts, the enrolment of a further 8 patients has been deemed appropriate, reaching an estimate of 24 subjects per group. Thus, 48 patients will be enrolled starting from the date of Ethical Committee approval, within July 2024. The sample size has been estimated using G*Power software (38).

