**Methods:**

Single-center, randomized controlled single-blind trial comparing TT + AVR vs. TT in II-III stage PD patients with gait disturbances. Assessment will be performed at baseline (T0), end of training (T1), 3 (T2) and 6 months (T3, phone interview) from T1. The primary outcome is difference in gait performance assessed with the Tinetti Performance-Oriented Mobility Assessment gait scale at T1. Secondary outcomes are differences in gait performance at T2, in balance and spatial–temporal gait parameters at T1 and T2, patients’ satisfaction and adherence. Changes in falls, functional mobility, functional autonomy, cognition, mood, and quality of life will be also assessed at different timepoints. The G*Power software was used to estimate a sample size of 20 subjects per group (power 0.95, *α* < 0.05), raised to 24 per group to compensate for potential drop-outs. Both interventions will be customized and progressive, based on the participant’s performance, according to a predefined protocol.

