### Outcome measures

2.6

The primary outcome is the difference in gait performance assessed by the POMA-G scale between the TT+AVR and the TT group at T1. The secondary outcomes are differences in mobility (measured by POMA-G at T2 and POMA-B at T1 and T2), in kinematic gait parameters assessed at T1 and T2, measured by the Optogait system, differences in other motor and non-motor symptoms at T1and T2, patients’ satisfaction, assessed with a 5-point Likert scale, and adherence to the treatment.

Exploratory outcome measures include changes in NfL concentration and change in individual Raman spectra of blood-derived cEVs before and after treatment. The correlation between Raman spectra of blood cEVs and the rehabilitation outcome will be assessed (the biological characterization of patients at T0 analyzing cEVs performed by Raman Spectroscopy will provide numerical scores that will be correlated with motor parameters obtained after treatment to identify prognostic biomarkers of rehabilitation outcome).

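### Minor arithmetic slip in the dropout allowance: at around 20% dropout, 24 per arm leaves about 19 evaluable per arm, just under the 20 that the power calculation needs

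*Protocol article*

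**What the plan says.** Section 2.2 (Sample size estimation) of the protocol article sizes the trial on the between-arm comparison of POMA-G at the end of training. Section 2.6 names the same endpoint: "The primary outcome is the difference in gait performance assessed by the POMA-G scale between the TT+AVR and the TT group at T1".

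The planning values come from an earlier study of partial weight-supported treadmill training: "Mean values observed in the POMA-G score after 4 weeks of treatment were 10.7 ± 1.1 and 11.7 ± 0.5", "leading to a high effect size *d* = 1.17". With 95% power and alpha 0.05, section 2.2 arrives at 20 subjects per arm.

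The section then turns to losses: "Dropouts are expected to be around 20" per cent. The response is that "the enrolment of a further 8 patients has been deemed appropriate, reaching an estimate of 24 subjects per group", so 48 are to be enrolled.

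The Methods part of the abstract gives 20 per group with power 0.95, "raised to 24 per group to compensate for potential drop-outs". It gives no dropout rate.

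**The concern.** An allowance for dropout has to leave the required number evaluable after the losses, and the losses are a fraction of the patients enrolled. The increase in section 2.2 equals 20% of the evaluable number (40 × 0.20 = 8), so the percentage has been applied to the wrong base. Section 2.3 counts participants who miss more than 5 sessions as dropouts and excludes patients for insufficient adherence. Those losses fall before the primary assessment at T1, so they bear directly on the primary comparison.

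What is at stake is whether the enrolment target matches the plan's own assumptions. The 20 per arm carries no reserve, because the computed power there is 95.0% with nothing to spare. Any shortfall below 20 therefore takes power under the planning target, though only slightly.

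**Working it through.** **Inputs, all from section 2.2:** means 10.7 and 11.7; SDs 1.1 and 0.5; alpha 0.05; power 95%; 20 per arm required; dropout around 20%; 24 per arm and 48 in total enrolled. The section does not say whether the test is one- or two-sided.

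**Step 1. Reproduce the effect size.**
- Pooled SD = √[(1.1² + 0.5²)/2] = √0.73 = 0.854.
- d = (11.7 − 10.7)/0.854 = 1.17, as stated.

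**Step 2. Reproduce the 20 per arm.** For a two-sample t-test with n per arm, degrees of freedom are 2n − 2 and the noncentrality parameter is d√(n/2). At n = 20 this is 1.17 × √10 = 3.70.
- Two-sided: power is 0.9500 at n = 20 and 0.9392 at n = 19, so 20 is the smallest n that reaches 95%. This matches the plan.
- One-sided: 17 per arm would be enough, which does not match.

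The two-sided reading is used below.

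**Step 3. Reproduce the 24 per arm.**
- 20 × (1 + 0.20) = 24, as stated.
- 20/(1 − 0.20) = 25, which is the number that leaves 20 after a 20% loss.

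**Step 4. What 24 per arm delivers.**
- Evaluable at 20% dropout: 24 × 0.80 = 19.2 per arm; 48 × 0.80 = 38.4 in total, against 40 needed.
- Dropout that 48 enrolled can absorb while 40 remain: 8/48 = 16.7%.
- Shortfall in enrolment: 25 − 24 = 1 per arm, 2 in total.

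**Step 5. Power at the resulting numbers (two-sided t-test, alpha 0.05, d = 1.17).**

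| Dropout from 24 per arm | Evaluable per arm | Power |
|---|---|---|
| 15% | 20.4 | 95.4% |
| 16.7% | 20 | 95.0% |
| 18% | 19.7 | 94.7% |
| 20% | 19.2 | 94.2% |
| 20%, rounded down to whole patients | 19 | 93.9% |

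**The case against.** The case for leaving the text alone rests on four points.

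**The rate is approximate.** Section 2.2 says around 20%, and 16.7% could be called around 20%. This limits how much weight the point can bear. It does not explain the figure, because 8 is exactly 20% of 40 and the section offers no other derivation.

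**The loss of power is trivial.** This stands. About one percentage point is lost, and power stays near 94%. The same loss would follow if the true d were 1.14 instead of 1.17 with 20 per arm (power 94.0%). The planning d also comes from a different contrast, partial weight-supported treadmill training against conventional gait training, so its own uncertainty far exceeds this gap.

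**No power is claimed for 48 enrolled with 20% lost.** This also stands. A reader might infer that the trial fails to deliver its stated power. The documents do not support that: both section 2.2 and the abstract attach the 95% to 20 subjects per arm, and that figure reproduces exactly. What fails is the step from 20 to 24.

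**Chance of falling short.** A reader might also treat each dropout as an independent 20% event and find only a 21% chance of at least 20 completers in both arms, or a 36% chance of at least 40 overall. Those figures do not measure the slip. With 25 per arm the same chances are only 38% and 58%, so most of the apparent risk is ordinary random variation that any allowance built on expected dropout leaves in place.

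**Conclusion.** The point holds as a minor arithmetic error in section 2.2. The allowance was formed by multiplying the evaluable number by 1.20 when it should have been divided by 0.80. At the expected dropout, 48 enrolled leaves about 19 evaluable per arm, one short of the plan's own requirement, and power is about 94% where 95% was intended.

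The shortfall in evaluable numbers rests only on the document's 20 per arm and its dropout rate taken at 20%. The power figures also assume a two-sided t-test at alpha 0.05, which the section does not state but which reproduces its 20 per arm, and d = 1.17. If dropout is 16.7% or lower, there is no shortfall. Nothing here calls the design, the analysis or the trial's ability to detect the planned effect into question.

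**What to change.** Amend section 2.2 to say that enrolling 48 allows for about 16.7% dropout, and that at 20% dropout about 19 per arm would be evaluable, giving about 94% power at d = 1.17 with two-sided alpha 0.05. This costs one sentence and no patients. If the sponsor prefers to keep 20 evaluable per arm at 20% dropout, the target becomes 25 per arm, 50 in total, which is two more patients.

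With the first option the abstract need not change, since it gives no dropout rate and ties the 0.95 power to 20 per group. With the second, its 24 per group would become 25.

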### Inclusion and exclusion criteria

2.3

Individuals with idiopathic PD consecutively referring for counseling and outpatient rehabilitation management will be included, if they fulfill the following inclusion criteria:

diagnosis of PD according to the POSTUMA diagnostic criteria (39), in II-III Hoehn and Yahr stage (35), in stable drug therapy for at least 1 monthage more than 18gait disturbanceability to walk for at least 5 min without assistancewilling to participate in the study and ability to understand and sign informed consent

Individuals will be excluded in the presence of:

other pathologies able to interfere with motor skills as symptomatic arthritis involving hip/knee/ankle, stroke outcomes or severe polyneuropathycognitive impairment potentially interfering with rehabilitation procedures, estimated as a corrected score of less than 18.58 at the Montreal Cognitive Assessment (MoCA) (40)hallucinations and other psychiatric disorders not controlled by drug therapy, as in case of alcohol or drug abuseuncompensated visual/auditory deficit that limits the enjoyment of the cues provided by the AVRcommunication deficit from any cause that impairs understanding of the task and the objectives of the interventionmedical conditions hindering the effect of the training as severe orthostatic hypotension and severe cardiovascular diseases.

Patients undergoing other experimental protocols will also be excluded, whereas patients who regularly engage in physical activity or sport will not be excluded.

Pharmacological treatment is required to be stable until T1. During the study, patients will be excluded in case of insufficient adherence to the intervention according to the study procedures. Missing up to 5 sessions is allowed, and lost sessions will be possibly made up at the end of treatment. Participants who miss more than 5 sessions will be considered dropouts.

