Regarding non-motor symptoms, cognitive impairment may associate or even precede motor symptoms in PD and can worsen over time from mild cognitive impairment to full-blown dementia during the disease course. Drugs give limited benefits to this disorder, making it essential to explore the effects of non-pharmacological approaches (13). Targeted cognitive training presents some evidence of effectiveness in patients with initial impairment, but a recent review suggests that TT produces even greater cognitive effects (14). Virtual reality (VR) is used in the motor and cognitive training of patients with various neurological diseases, including PD. VR refers to a computer-generated three-dimensional digital environment that can be explored and interacted with by a person. Augmented reality or augmented virtual reality (AVR) is the union between VR and real life. The person who experiences it can interact with virtual content in the real world. Computer-generated content is superimposed on reality through visual stimuli such as objects and films, tactile and olfactory sensations, and sounds. AVR is proposed as an interactive approach, that aims to amplify the effects of motor training, both directly and indirectly, increasing the patient’s motivation and satisfaction, promoting greater adherence and participation to treatment, and training also cognitive aspects of fall risk (14). For these reasons, AVR is considered an emerging and promising therapeutic tool in neurorehabilitation (15). In this regard, positive results emerged from the clinical trial of Gulcan et al. (16) in which AVR-VR TT has been demonstrated to be effective in PD on most of spatial–temporal gait parameters compared to conventional physical therapy.

Moreover, results from recent reviews dedicated to comparing the benefit of VR rehabilitation, including TT, versus conventional one showed that VR appears to be promising in motor outcomes such as gait and mobility (17–19), obtaining the most replicated and convincing result on balance (18–21); less evidence has been reported on functional autonomy (19) and QoL (18).

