### Interventional protocol

2.5

Intervention in both groups will be performed using the Motek’s C-Mill, with three sessions of treadmill training per week, every day at the same time during the “on” period of the participant, for 8 weeks. Participants will be encouraged to avoid using the side support bars during training, but a brief period (15-min) of familiarization with the task, during which intermittent support on the bars will be allowed, will be conducted during the first three sessions before starting the training. For all subjects, the training will be customized and progressive in gait speed and duration; for the experimental group, the difficulty of AVR applications will also gradually increase. The progression will be based on the participant’s level of performance, but will follow fixed predetermined rules. In detail, gait speed will be set at 80% of the individual’s overground walking speed at the beginning of training, and will be weekly increased by 10% to a maximum of 120% of that speed; at the beginning of training, the training duration will be 25 min, including 5 slots of exercise lasting 5 min, with a 4-min rest between each slot; every 2 weeks it will be increased by 1 min per slot, until a maximal duration of 45 min in the last 2 weeks of treatment. However, the progression will be applied considering the subject’s tolerance, i.e., the ability to keep the heart rate within safety limits and without subjective discomfort, and to walk without having to brace on the side bars.

Participants assigned to the experimental group will exercise five AVR applications (one for each slot of training): “nature island,” “stepping stones,” “walking area,” “obstacles avoidance,” and “tracks.” These applications train balance and changes in walking speed, promote gait adaptation strategies and strategies to overcome freezing of gait, in a safe and controlled environment; moreover, information to promote proper walking is provided, including feedback on gait parameters such as stride length, cadence and symmetry. Five difficulty levels will be prepared for each C-Mill application, with transition between levels set at a success rate of 80%.

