Pain is a frequent non-motor symptom in PD, contributing significantly to disability and reduced QoL. It affects around 67.6% of PD patients versus 15–30% of the general population. The most frequent pain syndromes in PD are musculoskeletal pain, neuropathic radicular pain, dystonia-related pain, akathitic discomfort, and primary central parkinsonian pain (78). Among clinical scales suitable to assess pain intensity, the NRS scale is simple, well-validated, and easy to use for clinicians and to understand for patients. The NRS is a recommended tool for assessing pain intensity in the general population and is widely used also in PD, although it is cautiously recommended in this population because it is not disease-specific (78).

Experience appreciation will be estimated for both treatment groups using a 5-point Likert scale and correlated with the level of adherence to the treatment. Indeed, independently of the effectiveness on motor symptoms, results coming from previous studies suggest a higher appreciation of VR training by the patients compared to the conventional TT which is perceived as monotonous or boring, and less useful to integrate into their daily life environment (79–81). Thus, satisfaction will be tested to confirm these findings. Along with adherence to either treatment, and to the evaluation of the possibly different clinical and instrumental effect of either intervention, this measure can provide relevant information on potential barriers and motivators for exercise and rehabilitation. Indeed, as to accessibility to these services, while the TT is currently available in most rehabilitation facilities, TT associated to AVR is more expensive and less available. As to motivators, AVR is claimed to be a relevant motivator (14): our study will allow us to investigate this issue, by allowing a comparison of both adherence and patients’ satisfaction in either intervention. Thus, our study may provide highly relevant information about the superiority of TT + AVR versus TT, to potentially provide grounds to expand the adoption of TT + AVR instruments, even if this may be associated to generally higher costs.

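### Randomised participants who miss more than 5 of 24 sessions are excluded as dropouts, so the primary comparison appears restricted to adherent participants and may be biased if exclusion differs by arm

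*Protocol article*

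**What the plan says.** **The rule.** Protocol article, section 2.3: during the study, "patients will be excluded in case of insufficient adherence to the intervention according to the study procedures". The threshold follows: "Participants who miss more than 5 sessions will be considered dropouts". Up to 5 missed sessions are tolerated, and lost sessions may be made up at the end of treatment.

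**The number of sessions.** Section 2.5 plans "three sessions of treadmill training per week" for 8 weeks in both arms.

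**The sample size.** Section 2.2 arrives at 20 per arm, expects about 20% dropout and raises enrolment to 24 per arm to compensate.

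**The analysis.** Section 2.7.2 names a two-way repeated measures ANOVA (time by group) for primary and secondary outcomes. No analysis set is named, and nothing is said about assessing or analysing participants excluded under section 2.3.

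**Adherence as a question of the trial.** The Introduction describes AVR as an approach aimed at "promoting greater adherence and participation to treatment". Section 2.6 lists among the secondary outcomes patient satisfaction, "assessed with a 5-point Likert scale, and adherence to the treatment". The Discussion says the study will examine AVR as a motivator "by allowing a comparison of both adherence and patients’ satisfaction in either intervention".

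**The concern.** Sessions take place only after allocation, so the rule removes randomised people for something they did after randomisation. If those removed differ between arms in number or in kind, the remaining groups are no longer comparable by design, and a POMA-G difference at T1 can arise without a treatment effect, or a real one can be masked.

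Many trials carry this risk, but this one has a particular reason to take it seriously. Better adherence is one of the ways in which AVR is thought to work, and the trial sets out to compare adherence between arms. Equal exclusion cannot be assumed while that question is open.

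Two secondary outcomes are also touched. Satisfaction is asked only at T1, so it would come mainly from those retained. Adherence would be truncated from below if it were reported only for retained participants.

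The article itself fixes the exclusion rule, so this is more than a detail left to an analysis plan. If exclusion also ends assessment, no later analysis plan can recover T1 and T2 data that were never collected.

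**Working it through.** **1. Threshold.** 3 sessions × 8 weeks = 24 sessions. 24 − 5 = 19, and 19/24 = 79%. This assumes that a made-up session does not cancel a missed one; section 2.3 does not say.

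**2. The plan's own sample size.** Inputs from section 2.2: means 10.7 (SD 1.1) and 11.7 (SD 0.5), power 95%, alpha 0.05.
- Pooled SD = √[(1.1² + 0.5²)/2] = 0.854; d = 1.0/0.854 = 1.17.
- Two-sided two-sample t-test: 20 per arm gives power 95.0%.

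The stated 20 per arm reproduces. The difficulty is who is compared, not this arithmetic.

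**3. Who reaches the analysis.** Four points lead the same way: participants are excluded (2.3); they are called dropouts (2.3); enrolment is raised to make up for dropouts (2.2); and a repeated measures ANOVA in its standard form drops anyone lacking a time point (2.7.2). No passage points the other way. Extra enrolment restores numbers but does not undo selection.

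**4. Size of the possible bias.** The documents give neither exclusion rates by arm nor the relation between attendance and outcome, so both are assumed. Model: no true effect; 24 randomised per arm; normal T1 outcome; a latent attendance score with correlation ρ to the outcome; the lowest fraction p of attenders excluded in each arm; t-test at T1. The mean shift among those retained, in SD units, is ρ·φ(z_p)/(1 − p), where z_p is the p-quantile of the standard normal and φ its density. The bias is the difference between arms.

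Values of φ(z_p)/(1 − p): 0.109 at p = 5%, 0.195 at 10%, 0.274 at 15%, 0.350 at 20%, 0.424 at 25%, 0.497 at 30%, 0.570 at 35%.

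| Excluded, one arm v other | ρ | Bias (SD) | POMA-G points (× 0.854) | Two-sided type I error (simulated) |
|---|---|---|---|---|
| 20% v 20% | any | 0 | 0 | about 5% |
| 25% v 15% | 0.5 | 0.5 × (0.424 − 0.274) = 0.07 | 0.06 | about 5.5% |
| 30% v 10% | 0.5 | 0.5 × (0.497 − 0.195) = 0.15 | 0.13 | about 7.7% |
| 35% v 5% | 0.7 | 0.7 × (0.570 − 0.109) = 0.32 | 0.28 | about 18% |

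Every row averages 20% loss. Over ρ from 0.3 to 0.7, the 30% v 10% split gives 0.09 to 0.21 SD, and the 35% v 5% split gives 0.14 to 0.32 SD.

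**5. Direction.** If poor attenders do worse (ρ > 0) and more of them leave the control arm, the retained controls look better than they should and the bias runs against AVR. With ρ < 0 it reverses.

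**6. Price of keeping everyone.** Suppose a fraction q is non-adherent and gains none of the d = 1.17 benefit, and all are assessed. The diluted effect is 1.17 × (1 − q).

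| q | Diluted d | Power at 24 per arm | n per arm for 95% power |
|---|---|---|---|
| 10% | 1.05 | 94.6% | 25 |
| 20% | 0.94 | 88.8% | 31 |
| 30% | 0.82 | 79.3% | 40 |

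**The case against.** **The analysed set is not stated.** A reader might take it as settled that the primary analysis contains only adherent participants. The article does not say so; it names no analysis set, and a full protocol or analysis plan may treat dropouts differently. This stands, and is why the point says the comparison appears to be restricted. What remains is a written instruction to exclude, with nothing to offset it.

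**A difference in adherence is a hypothesis.** A reader might infer that the authors predict more exclusion in the control arm. They describe greater adherence as an aim of AVR and as a matter to investigate. The remark that conventional treadmill training is found monotonous concerns appreciation, not attendance. This stands; the claim is only that exclusion may differ.

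**The adherence outcome is not necessarily lost.** One might conclude that reported adherence can never fall below 79%. Applying the rule requires counting missed sessions in everyone, so attendance up to exclusion is known and the number excluded per arm is itself informative. Truncation follows only if adherence is reported for retained participants alone.

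**The numbers are assumed and can be modest.** A 25% v 15% split moves POMA-G by about 0.06 points, against a planning difference of 1.0. The scenarios also assign the whole 20% loss to this rule. Moreover, with poor attenders doing worse and leaving control more often, nearly all the excess rejections favour control: false findings for AVR fall below 1% at 30% v 10% (ρ = 0.5), against a nominal 2.5%. All of this is correct. It limits the size of the problem and shows that a false claim for AVR is not the main risk in that direction, but masking a real benefit is also an error, and the sign is not known in advance.

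**Conclusion.** The point holds in a qualified form. The article prescribes post-randomisation exclusion for low attendance, counts those excluded as dropouts, and nowhere keeps them in assessment or analysis. On the text available, the primary comparison appears to be among adherent participants, in a trial where adherence is an outcome and may plausibly differ by arm.

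The bias is nil with equal exclusion and ranges from about 0.07 to 0.32 SD across the three unequal splits tabulated, with type I error from about 5.5% to 18%. These figures illustrate what could happen; they do not predict it. The upper end needs both a strong imbalance and a strong link between attendance and outcome. The documents do not support saying that the trial will be biased, or that it will be biased in favour of AVR.

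Two smaller matters stand alongside. Satisfaction at T1 would come mainly from those retained, and it is unclear whether a made-up session still counts as missed.

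**What to change.** - Separate stopping training from leaving the study. Invite every randomised participant to T1, T2 and the T3 telephone interview, whatever their attendance. Reserve the word dropout for those who withdraw from assessment.
- Analyse all participants in their randomised arm, with a method that tolerates missing visits, such as a linear mixed model with the same time and group factors.
- Keep the set with no more than 5 missed sessions as a labelled per-protocol sensitivity analysis.
- Report adherence as sessions attended out of 24 for all randomised participants, together with the number per arm beyond the threshold.
- State how made-up sessions count, both for the threshold and for the adherence outcome.

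The training itself need not change. The cost is a short amendment, a few extra visits, and an estimate that includes partly trained participants. The dilution is not trivial: at 20% or 30% non-adherence, on the no-benefit assumption above, 24 per arm gives about 89% or 79% power. The stated 95% should be qualified accordingly, or the sample size reconsidered.
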